**Methods:**

To evaluate the complex healthcare intervention “SAFE BIRTH” we will conduct a cluster-randomized controlled stepped-wedge trial in five prenatal medical outpatient offices and eight non-metropolitan hospitals in Saxony, Germany. The offices and hospitals will be randomly allocated to five respectively eight sequential steps over a 30-month period to implement the telemedical IB. We define one specific primary process outcome for each IB (for instance IB#1: “*Proportion of patients with inclusion criterion IB#1 who have a prenatal care plan and psychosocial counseling within one week”*). We estimated a separate multilevel logistic regression model for each primary process outcome using the intervention status as a regressor (control or intervention group). Across all IB, a total of 1,541 and 1,417 pregnant women or newborns need to be included in the intervention and control group, respectively, for a power above 80% for small to medium intervention effects for all five hypothesis tests. Additionally, we will assess job satisfaction and sense of safety of health professionals caring for newborns (questionnaire survey) and we will assess families’ satisfaction, resilience, quality of life and depressive, anxiety and stress symptoms (questionnaire surveys). We will also evaluate the cost-effectiveness of ”SAFE BIRTH” (statutory health insurance routine data, process data) and barriers to its implementation (semi-structured interviews). We use multilevel regression models adjusting for relevant confounders (e.g. socioeconomic status, age, place of residence), as well as descriptive analyses and qualitative content analyses.

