Primary hypothesis: The intervention bundles (IB) of the HCNSB improve care close to home compared to current routine care.

Secondary hypotheses:

The IB increase job satisfaction and the feeling of safety of health professionals caring for premature and sick newborns. IB furthermore increase patients’ and families’ satisfaction with care, resilience and quality of life and reduce depressive, anxiety and stress symptoms.The IB are cost-effective from a statutory health insurance (SHI) perspective.

Qualitative research questions:

Which barriers hinder health professionals, pregnant women and families of newborns to use the IB?How do the IB influence the satisfaction and sense of safety of health professionals? How do they influence the patients’ sense of safety?

A cluster-randomized controlled stepped-wedge design (SW-cRCT) was chosen to investigate the hypotheses and research questions. Randomization will be performed at the hospital respectively outpatient office level.

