### Eligibility criteria

All patients or newborns meeting the following criteria will be included:

IB#1: Pregnant women with a disorder affecting fetal health (e.g. gestational diabetes) or with a suspicion of a serious disease of the fetus who are cared for on an outpatient basis by a participating prenatal obstetrician,IB#2: Newborns cared for in the delivery room or admitted as inpatients who required resuscitation or intensive care at the participating hospital,IB#3: Newborns admitted as inpatients who receive antibiotic therapy at the participating hospital and/or have a positive microbiologic screening result,IB#4: Premature or sick newborn receiving inpatient care at a participating hospital or the PC-UKD with a suspected need for transfer to the PC-UKD or indication for transfer back close to home,IB#5: Families of newborns hospitalized at a participating hospital for more than 5 days.

The secondary study population consists of outpatient obstetricians and health professionals at the hospitals using IB.

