#### Intervention bundle #4: Inter-facility transfer of premature and sick newborns

Once the child is stable and no longer needs the highly specialized neonatal care, it is the aim to transfer them close to home. However, this requires a continuous trans-institutional care and that the parents are appropriately prepared [4].

IB#4 provides support to participating hospitals via neonatal tele-consultations and as part of remote neonatal jour fixes. Through the regular exchange of information about neonates who are eligible for transfer close to home, **transfers from the PC-UKD to the hospitals will be promoted and transfers to the PC-UKD will be reduced**. The transfer process to the participating hospitals is accompanied by psycho-social support services and the parents are involved in these joint “remote rounds” in order to reduce uncertainties and enable an optimal flow of information. The jour fixes also serve as quality assurance measure by debriefing children who have already been transferred.

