### Assignment of interventions

The decision whether a newborn/patient is assigned to the intervention or control group depends on the time of inclusion. If the recruiting facility is in the control phase, the patient or newborn is assigned to the control group, otherwise to the intervention group. There is no blinding. The order in which the recruiting facilities enter the intervention phase is randomized. Figure 3 illustrates the allocation of clinics and prenatal medical outpatient offices to the intervention time points defined within the 30-month observation period.

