### Data analysis

As part of the confirmatory analysis, we examine the effectiveness of the intervention bundles using the IB-specific primary outcomes (Chap. 2). A separate logistic multilevel regression model is estimated for each primary outcome, which contains the intervention status (control or intervention phase) of the respective patient or newborn facility as an explanatory variable. The coefficient of this explanatory variable represents the intervention effect. To account for the clustered structure and the possible correlation of patient outcomes within the institutions, all models contain a random intercept at the institutional level [16]. The estimation results support the respective primary hypothesis if the estimated intervention effect is positive and statistically significant. Significance is tested using a two-tailed test with a significance level of 5%. To control for the inflation of the Type 1 error in our setting where we conduct multiple tests, Holm-Bonfferoni correction is used [17].

For testing of hypothesis 1, we compare data for the control and intervention group by analyzing frequencies and mean values, confidence intervals and conducting adjusted regression models.

The qualitative semi-structured interviews will be audio recorded and transcribed verbatim. The transcripts will be analyzed content-analytical using inductive and deductive coding.

Secondary hypothesis 2 (health economic evaluation) will be assessed by analyzing statutory health insurance routine data for each patient case. For each intervention bundle, we sum up the inpatient costs and costs for transfers of the individual patients, and, if mother and child are insured by AOK Plus, costs associated to their newborns in the context of their birth and costs in the 6 months following birth. In the next step, we compare average costs between the intervention and control phase cases and determine the difference in costs. Additionally, we compare the following aspects between the control and intervention group: patient transfers; length of inpatient stays; risks, complications and expenses during the inpatient stay; and more frequent clinic presentations. Expenses for patients and the medical staff involved will be included in the analysis (Table 1, last line).

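### The IB#1 cost comparison takes in newborn costs that depend on the hospitals' own concurrent rollout, and Table 1 lists no such costs for IB#1

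*Protocol article*

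**What the plan says.** All places are in the protocol article.

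- **Data analysis, secondary hypothesis 2:** for each bundle, the patients' inpatient and transfer costs are summed. If mother and child are both insured by the participating fund, the sum also takes in "costs associated to their newborns in the context of their birth and costs in the 6 months following birth". Average costs are then compared between intervention-phase and control-phase cases, and the difference is taken. No adjustment of this contrast is named.
- **Assignment of interventions:** "If the recruiting facility is in the control phase, the patient or newborn is assigned to the control group, otherwise to the intervention group".
- **Eligibility criteria:** IB#1 women are those "who are cared for on an outpatient basis by a participating prenatal obstetrician", so their recruiting facility is the office. The hospital bundles act elsewhere; IB#2, for example, covers "Newborns cared for in the delivery room or admitted as inpatients who required resuscitation or intensive care at the participating hospital".
- **Abstract, Methods:** "The offices and hospitals will be randomly allocated to five respectively eight sequential steps over a 30-month period". These are two separate step sequences in one time window.
- **Intervention bundle #4:** the aim is that "transfers from the PC-UKD to the hospitals will be promoted and transfers to the PC-UKD will be reduced". Transfers are an item in the cost sum.
- **Table 1, Economic impact:** the IB#1 rows hold maternal and pregnancy items, with inpatient costs limited to the mother in the six months before birth. The child's inpatient costs up to six months after birth stand under IB#2–5.

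**The concern.** A woman included for IB#1 carries the label of her office's phase. Once her newborn's costs enter the IB#1 total, part of the outcome arises in a hospital whose phase that label does not capture. The two labels are not independent over the trial: later inclusion makes it more likely both that the office has switched and that the birth hospital has. A raw difference in mean cost by office phase therefore mixes the effect of IB#1 with part of any effect of IB#2–5 on newborn costs.

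The Background says the evaluation will weigh heavily in deciding which innovations the statutory insurers reimburse. A cost figure labelled IB#1 that belongs partly to other bundles would misinform a bundle-by-bundle decision. In addition, the text and Table 1 disagree on whether newborn costs belong to IB#1 at all, so two analysts could report different IB#1 cost results from the same plan.

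**Working it through.** The document gives no figure for the cost comparison, so there is none to reproduce. The check asks how far hospital-bundle exposure differs between the two IB#1 groups.

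**Inputs from the document:** 5 offices in 5 steps; 8 hospitals in 8 steps; 30 months; IB#1 status set by office phase at inclusion.

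**Assumptions (not in the document; the schedule figure is not shown):** evenly spaced switches, with offices at months 5, 10, 15, 20 and 25 and hospitals every 30/9 = 3.33 months from 3.33 to 26.67; uniform inclusion; no link between the office order and the hospital order; birth a fixed lag L after inclusion.

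**Formulas.** Let s_O(t) be the share of offices switched at inclusion time t, and s_H(t+L) the share of hospitals switched at birth.

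- Exposure in the IB#1 control group: E_c = Σ(1 − s_O)·s_H / Σ(1 − s_O)
- Exposure in the IB#1 intervention group: E_i = Σ s_O·s_H / Σ s_O
- Gap: g = E_i − E_c

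**Result for births at participating hospitals, 30 months of inclusion:**

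| Lag L (months) | E_c | E_i | g |
|---|---|---|---|
| 2 | 35.5% | 77.8% | 42 points |
| 3 | 39.5% | 80.5% | 41 points |
| 4.5 | 44.9% | 84.1% | 39 points |

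Both groups are mixtures, and the intervention group is the more exposed.

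**Other assumed schedules (29 months of inclusion, lag 0 and 4 months):**

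| Offices / hospitals switch in months | E_c | E_i | g |
|---|---|---|---|
| 5–25 / 3.33–26.67 | 28%, 43% | 70%, 82% | 41, 39 |
| 6–24 / 6–24 | 24%, 39% | 75%, 86% | 51, 47 |
| 3–27 / 3–27 | 31%, 46% | 66%, 79% | 35, 33 |
| 6–18 / 6–24 | 14%, 29% | 72%, 85% | 58, 56 |
| 9–21 / 9–21 | 16%, 33% | 83%, 94% | 68, 61 |

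The gap runs from 33 to 68 points and is positive throughout.

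**From exposure to cost.** Let D be the mean change in newborn cost when the birth hospital runs IB#2–5, averaged over all IB#1 newborns at participating hospitals. Let q be the share of IB#1 births at those hospitals, and θ the true IB#1 effect on newborn cost. The raw contrast then estimates θ + g·q·D. With θ = 0:

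- q = 1: 0.33·D to 0.68·D
- q = 0.5: 0.16·D to 0.34·D

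**What a time-adjusted model does.** The hospital-phase share was regressed on office phase over 3,000 random switch orders (L = 3 months).

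- Office effects only: coefficient 0.53, so removing differences between offices is not enough.
- Office and period effects: the coefficient averages 0. Its SD across switch orders is about 0.12, 0.18 and 0.23–0.24 if 50%, 80% and 100% of an office's women use one local hospital. These pairing shares are assumptions. With no pairing the coefficient is 0 for every order.

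Period effects thus remove the systematic part. What can remain is chance alignment in the one order actually drawn.

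**The case against.** **Table 1 may govern.** It lists no newborn cost for IB#1, and if it prevails the problem disappears. That is fair, but the Data analysis text says the opposite: IB#1 is the bundle whose patients are pregnant women, so the clause on their newborns applies to it. The disagreement is itself part of the point.

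**The size is uncertain.** This stands. The schedule is not shown. IB#1 is aimed at women needing control at the university perinatal centre, so the share delivering at the eight hospitals is unknown. IB#2–5 also reach only newborns who meet their criteria, which makes D smaller than the effect on a treated newborn.

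**A condensed article may leave covariates to the full plan.** Also fair, and the abstract's list of confounders is open-ended. But the article does fix the cost sum and a comparison of averages by phase. The point addresses that stated choice, not a missing detail.

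**Stronger readings that the documents do not support:**

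- A reader might infer that neither IB#1 group receives routine care after birth. Under the evenly spaced schedule with lags of 2–4.5 months, 55–64% of control births at participating hospitals precede that hospital's switch. Moreover, routine care is the comparator of the primary hypothesis ("improve care close to home compared to current routine care"); the economic hypothesis names none.
- A reader might infer that savings are credited to IB#1. The direction of any IB#2–5 cost effect is unknown.
- A reader might infer that the same cost change is counted twice in a total. No planned step adds cost differences across bundles.
- A reader might want to adjust for the actual birth hospital's phase. Table 1 makes the level of the birth facility an IB#1 outcome, so that would condition on something IB#1 may change.

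**Conclusion.** The point holds for the secondary economic analysis. As written, the IB#1 cost contrast includes newborn costs and compares raw means by office phase, so part of any IB#2–5 effect on those costs, in either direction, would be reported as an IB#1 effect. The fraction is about 0.4 under evenly spaced steps with all births at participating hospitals, 0.33–0.68 over the other schedules tried, and about half of that if half the births are there. All these fractions rest on assumed switch times, uniform inclusion and unlinked switch orders; only the positive sign of the gap was common to every schedule tried. Separately, and without any assumption, the Data analysis text and Table 1 disagree on whether newborn costs belong to IB#1. Nothing here shows bias in the primary process outcomes.

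**What to change.** 1. Reconcile the Data analysis section with Table 1 on which costs belong to IB#1.
2. Make the IB#1 cost result the maternal and pregnancy items of Table 1, and report newborn costs separately.
3. Where newborn costs are compared by IB#1 phase, replace the raw mean difference with a model that has office effects and calendar-period effects.
4. As a sensitivity analysis, add the phase, on the date of birth, of the hospital the woman would be expected to use, for example by place of residence at inclusion. Do not use the actual birth hospital.
5. Optionally, in the IB#2–5 cost models, add an indicator that the mother was included at an intervention-phase office, only where the records can be linked.

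The cost is a change of analysis wording and slightly wider intervals. Steps 1–4 rest on switch dates, inclusion dates, birth dates and residence, which the project holds or can reasonably be assumed to hold. Step 5 needs a link between newborn and mother's office that the article does not describe.

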**Economic impact**		
1	Number of duplicate clinic presentations: Referrals to the Perinatal Center of the University Hospital	project database
	Required travel distances to the medical examination at the Perinatal Center of the University Hospital: travel distance from the patient’s home to the university hospital and back	project database
	Inpatient costs of mother (for 6 months before birth)	SHI routine data of the participating health insurance company
	Number of transfers of the mother	SHI routine data of the participating health insurance company
	Costs of transports between hospitals	SHI routine data of the participating health insurance company
	Duration of inpatient stays of the mother (for 6 months before birth)	SHI routine data of the participating health insurance company
	Outpatient costs for gynecological specialists and prenatal physicians	SHI routine data of the participating health insurance company
	Periods of inability to work during pregnancy	SHI routine data of the participating health insurance company
	Expenditures during the inpatient stay of the mother (measured by OPS codes)	SHI routine data of the participating health insurance company
2–5	Inpatient costs of the child (up to 6 months after birth)	SHI routine data of the participating health insurance company
	Number of transfers of the child related to the inpatient stay at birth	SHI routine data of the participating health insurance company
	Costs of transports between hospitals	SHI routine data of the participating health insurance company
	Duration of ventilation time [hours] of the child	SHI routine data of the participating health insurance company
	Number of inpatient stays of the child (for the 6 months after first discharge after birth)	SHI routine data of the participating health insurance company
	Expenditures for the child during the inpatient stay (measured by OPS codes)	SHI routine data of the participating health insurance company

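### The cost-effectiveness hypothesis is assessed by a difference in average costs between phases that is not related to any effect and has no stated adjustment for calendar time

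*Protocol article*

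**What the plan says.** The Background section of the protocol article states secondary hypothesis 2: "The IB are cost-effective from a statutory health insurance (SHI) perspective". The Data analysis section describes how it is assessed:

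- **Sum per case:** "For each intervention bundle, we sum up the inpatient costs and costs for transfers of the individual patients". Newborn costs, at birth and over the following six months, are added under a condition: "if mother and child are insured by AOK Plus, costs associated to their newborns in the context of their birth".
- **Contrast:** "we compare average costs between the intervention and control phase cases and determine the difference in costs".
- **Consequences, compared in addition:** "patient transfers; length of inpatient stays; risks, complications and expenses during the inpatient stay; and more frequent clinic presentations".
- **Cost of the new care:** "Expenses for patients and the medical staff involved will be included in the analysis".

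Table 1 (Economic impact) also lists for IB#1: "Outpatient costs for gynecological specialists and prenatal physicians".

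Under Assignment of interventions, a case belongs to the control or intervention group according to the phase its facility is in when the case is included. For secondary hypothesis 1 the Data analysis section names adjusted regression models. For hypothesis 2 it names none.

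**The concern.** Cost-effectiveness is a statement about cost in relation to effect. The described result is a cost difference, with consequences reported beside it and no rule that joins the two.

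In a stepped-wedge trial, intervention cases come later on average than control cases. A contrast of phase means without a time term therefore attributes price growth, tariff changes and drifting practice to the intervention.

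For IB#1, what the per-case total covers also depends on who insures the child, and one cost category listed for that bundle is outside the stated sum.

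The Background section gives the evaluation a leading part in the reimbursement decision, and the abstract makes translation into routine care conditional on the network being both effective and cost-efficient. The cost result is one of those two conditions.

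**Working it through.** The article gives no figure for the cost comparison, so there is none to reproduce. Its sample size (1,417 + 1,541 = 2,958) and power statement concern the five primary process outcomes.

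**1. Hypothesis against analysis.** A cost difference settles the question only when one option dominates, for example lower cost with no worse effect. The Monitoring section says intervention patients get telemedicine on top of usual care, and the expenses of the new care are included. Higher cost with better process outcomes is therefore a realistic result, and the described analysis has no way to judge it.

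**2. Calendar gap between the groups.** Inputs from the abstract: 5 offices in 5 steps and 8 hospitals in 8 steps, over 30 months. Assumptions, because Fig. 3 is not shown: K + 1 equal periods for K sites, and constant, equal recruitment. Site k then spends k periods of length 30/(K + 1) in control, so

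- mean control date = 30(2K + 1) / [6(K + 1)]
- gap = 30 − 2 × mean control date, by symmetry

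| | Mean control date (months) | Mean intervention date (months) | Gap (months) |
|---|---|---|---|
| 5 offices | 30 × 11/36 = 9.17 | 20.83 | 11.67 |
| 8 hospitals | 30 × 17/54 = 9.44 | 20.56 | 11.11 |

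With switch dates spread evenly instead over months 1–29, 6–24, 3–18 or 12–27, the gap runs from 8.5 to 13.2 months.

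**3. Spurious difference with no intervention effect.** Formula: (1 + r)^(gap/12) − 1, with annual cost growth r assumed.

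| r | 5 offices | 8 hospitals |
|---|---|---|
| 2% | 1.9% | 1.9% |
| 3% | 2.9% | 2.8% |
| 5% | 4.9% | 4.6% |
| 8% | 7.8% | 7.4% |

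Across the other timings, the extremes for 3–5% growth are 1.03^(8.47/12) − 1 = 2.1% and 1.05^(13.23/12) − 1 = 5.5% of mean cost.

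**4. Does adjustment remove it?** A simulation with no intervention effect used 2,000 replicates per setting, log-normal costs with coefficient of variation 1.5, and site variation of 0.2 on the log scale. It had 5 × 6 × 10 = 300 or 8 × 9 × 4 = 288 cases. All settings are assumed.

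- At 3–5% growth, the unadjusted phase difference averaged 3.6–5.1% of the starting mean cost.
- With site and period terms, the average was within about 2% of zero, which is of the order of simulation noise.
- The standard deviation of the adjusted estimate was 32–37% of the starting mean cost.
- The unadjusted test rejected in 4.2–6.8% of replicates at 3–5% growth, so at this size the trend distorts the estimate more than the error rate.

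**5. Newborn costs in IB#1.** Let q be the share of cases with newborn costs and C the ratio of child to mother cost. The spurious difference relative to the control mean is (q_int − q_ctrl) × C / (1 + q_ctrl × C).

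- Equal shares in both phases: 0.
- Assumed shares of 45% (control) and 55% (intervention): 0.1/1.45 = 6.9% for C = 1, and 0.3/2.35 = 12.8% for C = 3.

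In IB#2 to IB#5, Table 1 lists the child's own inpatient costs, so the condition matters mainly for IB#1.

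**6. Outpatient costs in IB#1.** The stated sum covers inpatient and transfer costs. Table 1 lists outpatient gynaecological and prenatal costs for the same bundle, which is delivered through outpatient offices. A shift of cost into outpatient care would not appear in the total.

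**The case against.** The strongest reply is that this is a condensed article. A fuller health-economic plan may hold the cost model, the price year, a cost-effectiveness ratio and its uncertainty. The abstract says in general that multilevel models adjusting for confounders are used. That stands in part: the comparison cannot be called unadjusted as a settled fact. But the abstract's examples are socioeconomic status, age and residence, not calendar time. The Data analysis section names adjustment for hypothesis 1 and a difference in averages for hypothesis 2, and no model in the article, including the primary ones, has a stated time term.

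A reader might also infer more than the text supports:

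- **That effects are ignored.** They are not. Transfers, length of stay and complications are compared, and each bundle has a primary outcome. What is missing is a link between costs and any of these.
- **That intervention costs are omitted.** The article includes them.
- **That one saving is counted several times** when a newborn qualifies for several of IB#2 to IB#5. Costs are computed per bundle and the article nowhere adds the bundle totals. Overlap limits attribution to one bundle; it does not show double counting.
- **That the newborn-cost condition biases the result.** It does so only if the linked share differs by phase, and nothing in the article suggests that it does. The article also does not expressly say that linked and unlinked totals are averaged together.

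Finally, price growth alone could be removed by using one price year. That is correct, but it would leave trends in practice and volume in the contrast.

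**Conclusion.** The point holds in this limited form. The mismatch between the hypothesis and its analysis rests on the text alone. The confounding with calendar time follows from assignment by inclusion date together with the absence of a stated time term. Its size rests on assumptions: about 3–5% of mean cost for 3–5% annual growth under equal steps and constant recruitment, and 2.1–5.5% across the other timings tried. That is small beside the sampling error of a cost difference at these numbers, so it matters mainly for the reported estimate. For IB#1, the stated total lacks a fixed meaning and omits a listed cost; any resulting bias depends on a difference in linkage that is not known. This is a secondary hypothesis outside the confirmatory analysis. The change is worth making because it is cheap and the cost result bears on reimbursement.

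**What to change.** In the analysis plan for secondary hypothesis 2:

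1. Express all costs in one price year.
2. Estimate the phase difference with a model that contains period effects and a site effect.
3. For IB#1, report mother-only totals for all cases and mother-plus-child totals for linked pairs only, and include the outpatient costs listed in Table 1.
4. Relate the incremental cost, including the intervention expenses already planned, to the bundle's primary outcome, with an interval that respects clustering. Otherwise, restate the hypothesis as one of cost reduction.

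The components are already listed as collected, so the cost is wording and analysis work. The statistical price is wider intervals once period and site effects are fitted, and fewer cases in the linked mother-plus-child analysis.

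### The cost effect is a difference of phase averages with no calendar-time or site adjustment named, so any cost trend over the 11 to 12 months between phases enters it

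*Protocol article*

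**What the plan says.** The Data analysis section of the protocol article states that secondary hypothesis 2 "will be assessed by analyzing statutory health insurance routine data for each patient case". Inpatient and transfer costs are summed for each case, and then "we compare average costs between the intervention and control phase cases and determine the difference in costs". A further sentence begins "Additionally, we compare the following aspects between the control and intervention group" and lists transfers, length of stay, complications and related items, without naming a method. No site term, calendar term, price year or regression appears in that paragraph.

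The same section treats the other hypotheses differently. The primary outcomes get a logistic multilevel model with a random intercept for the institution. Hypothesis 1 is to be analysed by "analyzing frequencies and mean values, confidence intervals and conducting adjusted regression models".

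The abstract adds a general statement: "We use multilevel regression models adjusting for relevant confounders (e.g. socioeconomic status, age, place of residence), as well as descriptive analyses and qualitative content analyses". It does not tie these models to costs, and calendar time is not among its examples.

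On the design, the abstract has the sites "randomly allocated to five respectively eight sequential steps over a 30-month period". The section Assignment of interventions says: "The decision whether a newborn/patient is assigned to the intervention or control group depends on the time of inclusion". It also states that the order of switching is randomised.

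**The concern.** In a stepped wedge, phase is tied to calendar time by construction: every site contributes control cases first and intervention cases later. A plain difference between phase averages therefore includes whatever happened to costs over time, such as price rises, tariff changes or shifts in practice. The randomised order decides which site switches when. It does not change the fact that intervention cases come later.

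The two phases also weight the sites differently. Early-switching sites supply more of the intervention cases and late-switching sites more of the control cases. Randomising the order makes this imbalance zero on average, but one drawn order of 8 or 5 sites can still leave a sizeable difference, and a difference of averages does nothing to remove it.

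Cost-effectiveness is a named hypothesis, and the Background says the evaluation will weigh heavily in the reimbursement decision. Rising prices would count against the network and could hide a real saving. A falling trend, for example in length of stay, would do the opposite.

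**Working it through.** **Inputs from the protocol article.** Eight hospitals in eight steps, five offices in five steps, 30 months (abstract). Phase set by time of inclusion, switching order randomised (Assignment of interventions). Cost contrast as quoted (Data analysis).

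**Assumptions.** K sites, K+1 equal periods, equal and constant recruitment per site; the figure with the actual schedule was not available. Price growth and between-site cost spread are not in the document and are shown as ranges.

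**Plan's own figure.** None is given for costs. The stated totals allow one check of the layout: 1,417 / (1,417 + 1,541) = 47.9% control cases, close to the 50% of an evenly spaced stepped wedge.

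**Step 1: calendar gap between phases.** Site k switches at s_k = 30k/(K+1) months. Mean inclusion time of control cases = Σ(s_k²/2) / Σs_k. By symmetry, intervention cases lie at 30 minus that value.
- Hospitals: (30/9) × 204 / (2 × 36) = 9.44 months; intervention 20.56; gap 11.1 months.
- Offices: (30/6) × 55 / (2 × 15) = 9.17 months; intervention 20.83; gap 11.7 months.

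With the first switch moved over months 3 to 6 and the last over months 24 to 27, the gap is 10.9 to 12.7 months (hospitals) and 10.2 to 12.3 months (offices).

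**Step 2: price growth entering the difference.** (1 + r)^(gap/12) − 1:

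| Assumed growth per year | Hospitals | Offices |
|---|---|---|
| 2% | 1.9% | 1.9% |
| 3% | 2.8% | 2.9% |
| 5% | 4.6% | 4.9% |
| 8% | 7.4% | 7.8% |

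**Step 3: would a site term alone cure this?** No. Within a site that switches at month s, control cases centre on s/2 and intervention cases on (30 + s)/2, a gap of 15 months at every site. At 5% a year that is 1.05^(15/12) − 1 = 6.3%, more than the 4.6% of the plain difference for hospitals.

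**Step 4: site mix.** Site k has control weight k/Σk and intervention weight (K+1−k)/Σk.
- Hospitals: the first to switch gives 1/36 = 3% of control and 8/36 = 22% of intervention cases; the last gives the reverse. Root sum of squared weight differences: √168 / 36 = 0.360.
- Offices: √40 / 15 = 0.422.

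Over random orders, the site contribution to the cost difference has mean zero and SD 0.36 or 0.42 times the between-site SD. If mean cost varies between sites by 20% (assumed), that SD is 7.2% of mean cost for hospitals and 8.4% for offices; at 40% it is about 14% and 17%. Over the alternative schedules the multiplier ranges from 0.28 to 0.37 and from 0.38 to 0.51.

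**Step 5: simulation with no true effect.** Eight sites, 600 cases, within-site coefficient of variation 1.0, between-site 20%, prices rising 5% a year, 1,500 runs (all assumed):

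| Estimate | Average spurious difference |
|---|---|
| Difference of phase averages | +4.7% |
| Adjusted for site only | +6.1% |
| Adjusted for site and period | −0.4% |

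Across six scenarios the site-and-period estimate averaged between −0.4% and +0.6%. Without any trend, raising the between-site spread from 0 to 20% raised the SD of the plain difference from 8.1% to 11.0%, in line with step 4: √(8.1² + 7.2²) = 10.8.

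**The case against.** The best defence is that the article nowhere calls the comparison unadjusted. A difference in average cost can be the output of a regression, and the abstract's sentence on adjusted multilevel models comes right after its mention of the cost evaluation. Read that way, costs would have a site-level model. This reading is possible, and it would answer most of the site-mix point. It does not reach the time point: neither place names calendar time, and step 3 shows that a site term alone leaves the trend in and enlarges it. The contrast with hypothesis 1, where adjusted regression is named in the same section, also weakens this reading without settling it.

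A second defence is that this is a condensed article. Price year and interval method are commonly left to an analysis plan. That stands for those details. But the article does state how the cost effect is formed, and that statement does not suit the design.

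Several stronger readings are tempting, and the document does not support them:
- That site differences bias the cost result, or that the answer depends largely on which site drew which step. The order is randomised, so site mix is a zero-mean chance imbalance. Its size rests on a between-site spread the document does not give. For bundle 4, part of the cost arises at the one shared university centre, which may reduce that spread.
- That the cost interval will be too narrow. The cost paragraph specifies no interval or test. In the simulation, a 5% test treating cases as independent rejected in about 17% of runs, but the plan does not say it would use one.
- That the additional comparisons are also simple subtractions. Their method is not stated, and price growth cannot affect counts or durations.
- That the primary models are safe because they have a random intercept. They too name no calendar term.

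**Conclusion.** The point holds for calendar time as a systematic error and for site mix as a loss of precision. Followed as written, the cost rule places intervention cases about 11 to 12 months later than control cases, and any cost trend over that time is counted as an effect of the bundles. With assumed price growth of 3% to 5% a year, this adds about 2.8% to 4.9% to the intervention side. The direction follows from the design; the size depends on the assumed growth and on roughly equal periods and site volumes. Very unequal volumes would change both the gap and the weights.

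The change should be made, but it is not critical to the trial's main conclusion: costs are a secondary hypothesis with no stated test. Whether the abstract's models are meant to cover costs cannot be settled from the article.

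**What to change.** State in the Data analysis section, or in the analysis plan, that the cost difference is estimated from a model suited to skewed costs with terms for site and calendar period, on costs valued at one price year. Say explicitly whether the abstract's multilevel models apply to costs.

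Base inference on the randomised step order: permute the order, or use a small-sample cluster correction. Plain cluster resampling is weak with 5 or 8 sites. Permutation has its own limit for the offices: 5! = 120 orders, so no p-value below 1/120 = 0.008. For the hospitals, 8! = 40,320 orders are ample.

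Use site and period terms also for transfers, length of stay and complications, where price growth plays no part but other time trends can.

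The cost is a change of wording and a little more analysis work, with no new data. The downside is a wider interval than a comparison of averages would give.
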